##### Fisheries yield of mature fish

Trained field enumerators will record fish catches at landing sites (fishery-dependent data). The field team will ask permission to count and weigh a fisher's catch when they return from fishing. Upon consent, the enumerators will identify the fish species or genus level and measure the lengths of a sub-sample of the individuals (*n* = 20). Sampling will occur at least four times per month at randomly stratified days, as determined by the moon phase and considering dominant gear types. Monthly catch per unit effort (CPUE) will be determined as the mean daily catch multiplied by the fishing days per month. We will also evaluate species-specific length-frequency distributions to determine the yield of mature individuals. Sustainable yields will be determined by comparing the initial yields vs. the rate of change of yields for each landing site or BMU, based on average length of catch for given species.

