### Logic framework

Figure 1 illustrates the logical framework for our integrated nutrition and fisheries intervention We expect our nutrition social marketing campaign to increase consumption of fish among children under 5 and dietary diversity for households, leading to reduced enteric disease morbidities and reduced stunted growth and development. We anticipate modified fishing traps with escape gaps (to allow immature fish to leave the trap while retaining mature fish) to promote fisheries sustainability and increase fisher income, leading to greater harvest efficiency, improved resilience to environmental change, dietary diversification, and improved nutritional status through both direct consumption and indirect poverty reduction pathways.

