## Methods and analysis

### Design

We aim to test the effectiveness of the multi-component *Samaki Salama* intervention as it intersects with nutrition security and fisheries sustainability in Kilifi County, Kenya. Table 1 details the specific aims and hypotheses.

**Table 1 T1:** Study aims and hypotheses.

**Study aims**	**Hypotheses**
1. Determine the effects of a multi-component social marketing campaign to promote fish nutrition, dietary diversity, and food safety on child growth	**Primary** Hypothesis 1: Children in combined intervention groups have increased height-for-age *Z* by 0.2 compared to children in the control Hypothesis 2: Children in combined intervention groups have increased weight-for-age *Z* by 0.10 compared to children in the control Hypothesis 3: Children in combined intervention groups have increased fish food intakes by 100 g compared to children in the control
	**Secondary** Hypothesis 4: Children in combined intervention groups have increased dietary diversity by 1.2 compared to children in the control Hypothesis 5: Children in combined intervention groups have reduced diarrheal morbidity by 5 percentage points compared to children in the control
	**Exploratory** Hypothesis 6: Children in the social marketing + traps intervention group have increased dietary diversity and fish intake compared to children in the social marketing only group
2. Measure the impact of modified fishing traps with escape gaps on catch dynamics and earnings	**Primary** Hypothesis 7: Fishers in the social marketing + traps intervention group have significantly increased fisheries yields of mature fish compared to fishers in the control
	**Secondary** Hypothesis 8: Fishers in the social marketing + traps intervention group will have significantly increased earnings compared to fishers in the control

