**Primary outcomes**			
Child growth	Anthropometric measures of height and weight	Length-for-age *Z* score (LAZ) Weight-for-age *Z* score (WAZ) Weight-for-length *Z* score (WLZ)	Baseline, 12 mo.
Fish food intakes	24-h intake survey	Fish food intakes in g	Baseline, 12 mo.
Fisheries yield of mature fish	Fish catch survey at landing sites	Monthly catch per unit effort and fish size distribution	5–10 times per month at randomly stratified days over the course of 12 months

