### Analysis

#### Primary and secondary outcomes

Generalized linear regression modeling (GLM), allowing for non-normal distributions, will test the continuous outcomes of HAZ, WAZ, child dietary fish intake, child dietary diversity score, fisheries yield, and fish earnings. As a difference-in-difference analyses, change variables for each outcome will be examined (difference between baseline and endline). For the binomial outcomes of diarrhea morbidity (and other outcomes of stunting and underweight), we will estimate prevalence ratios by the GLM modeling with robust Poisson. If stunting prevalence in this population exceeds the acceptable threshold for use of odds ratios (0.2105), prevalence ratios (PRs) will be used to examine the intervention effect and were considered analogous to relative risk in this longitudinal study. The robust Poisson, with a classic sandwich estimator to correct the inflated variance of standard Poisson, is less affected by outliers.

To test for intervention effectiveness, the two intervention groups will be combined for all hypotheses except the secondary outcome of increased fisher earnings and exploratory hypothesis for differences between social marketing and social marketing + traps intervention groups. Regression models will be adjusted for potential confounding factors including age, sex of the child, corresponding baseline measures, and others found to differ significantly between the trial groups (e.g., maternal education). For fisheries yield, confounding factors will be used to adjust regression models, such as: water temperature, fishing ground area, coral cover, and seasonality. The *P* significance value for Type I error (and one-tailed test) will be *P* < 0.05 and corresponding 95% confidence interval. Diagnostics for regression model assumptions, structure and observations will be applied, and corrective procedures applied as necessary. If selection bias is widely detected with important differences across intervention and control communities, we will apply propensity score analyses (36). Data analyses will be performed with Stata software (version 16.0; StataCorp, College Station, TX) and R (4.1.2).

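### The quantity called monthly catch per unit effort is monthly catch of all sizes, and nothing says whether it or the length data tests Hypothesis 7 on mature fish

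*Protocol article*

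**What the plan says.** Hypothesis 7 (Table 1, primary, Aim 2) predicts that fishers in the social marketing plus traps group will have "significantly increased fisheries yields of mature fish compared to fishers in the control". For this outcome Table 5 lists the indicator "Monthly catch per unit effort and fish size distribution".

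The measurement section defines the first half: "Monthly catch per unit effort (CPUE) will be determined as the mean daily catch multiplied by the fishing days per month". The catch behind it is whatever is landed: "The field team will ask permission to count and weigh a fisher's catch when they return from fishing". No size or maturity limit is attached. Enumerators also "measure the lengths of a sub-sample of the individuals", with 20 given as the number.

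Maturity enters in the sentence after the formula: "We will also evaluate species-specific length-frequency distributions to determine the yield of mature individuals". No rule there or in the Analysis section joins these lengths to the catch formula.

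The Logic framework describes the escape gaps as designed "to allow immature fish to leave the trap while retaining mature fish". The Analysis section's example adjustment factors for yield are "water temperature, fishing ground area, coral cover, and seasonality". Fishing effort is not among them. Fisher revenue, by contrast, is expressed per fishing trip.

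**The concern.** There are two faults in one definition.

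- **Effort.** The label promises a rate per unit of effort, but the formula yields an amount that grows with effort. At a constant catch rate, fishers who go out more often score higher. That sits badly with the Abstract's rationale of greater harvest efficiency.
- **Maturity.** The formula counts all fish, while the outcome and Hypothesis 7 concern mature fish. The traps are meant to release immature fish, so the all-fish figure may fall when they work as designed. Hypothesis 7 predicts an increase and the Analysis section specifies a one-tailed test, so such a fall would count as no support for the hypothesis.

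With two indicators and no statement of which is decisive, the choice for a primary hypothesis could be made after the data are seen.

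**Working it through.** The plan has no figure to reproduce here. Its sample size rests on height-for-age, and Hypothesis 7 has no numeric effect size.

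**Units.** (catch ÷ day) × (days ÷ month) = catch ÷ month. A rate per unit effort would be total catch ÷ effort. If the daily mean is taken per fisher, the product is catch per fisher-month, which still scales with days fished.

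**Illustration.** All inputs are assumed. Let c = catch per fishing day (kg), d = fishing days per month and m = mature share by weight. Then:

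- stated indicator S = c × d
- catch per day R = (c × d) ÷ d = c
- mature catch per day M = c × m
- mature catch per month = c × m × d

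| Scenario | c | d | m | S | R | M | Mature per month |
|---|---|---|---|---|---|---|---|
| Base | 5.0 | 15 | 50% | 75 | 5.0 | 2.5 | 37.5 |
| 1. Same rate, more days | 5.0 | 20 | 50% | 100 (+33%) | 5.0 (0%) | 2.5 (0%) | 50 (+33%) |
| 2. Rate down 10%, more days | 4.5 | 20 | 50% | 90 (+20%) | 4.5 (−10%) | 2.25 (−10%) | 45 (+20%) |
| 3. Mature 2.5 to 3.0 kg/day, immature 2.5 to 1.25 kg/day | 4.25 | 15 | 3.0 ÷ 4.25 = 71% | 63.75 (−15%) | 4.25 (−15%) | 3.0 (+20%) | 45 (+20%) |

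Scenarios 1 and 2 show the effort fault: S rises while catch per day is flat or falling. Scenario 3 shows the maturity fault: S falls by 15% while mature catch rises by 20%, per day and per month alike. In scenario 3 plain catch per day also falls by 15%. Dividing by effort is therefore not enough, and the restriction to mature fish is needed as well.

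**The case against.** The strongest reply is that the formula is only half of the indicator. Table 5 pairs it with size distribution, and the very next sentence of the measurement section assigns the length data to mature yield, which is the Hypothesis 7 quantity. A reader might infer from the formula alone that the plan ignores maturity or cannot answer Hypothesis 7. The documents do not support that. What stands is narrower: the two halves are not combined, and neither is named as the test.

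Second, Hypothesis 7 speaks of yields, not yield per effort. A monthly mature total would be a legitimate target, and on that reading the rise in scenarios 1 and 2 is a true rise in monthly mature yield. This is right. It reduces the effort fault to a conflict with the label and with the efficiency rationale. It does not touch scenario 3, where the all-fish figure moves against mature yield on either scale.

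Third, the size is hypothetical. The effort fault matters only if days fished differ or change between groups, and nothing in the article says that they will. This also stands: the scenarios show possible direction, not expected bias.

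Fourth, a condensed article may leave the effort unit to the full protocol. That would excuse an omission. Here the formula is stated, and it contradicts its own label.

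A reader might also see a conflict between the minimum of four sampling occasions a month in the text and the 5–10 in Table 5. The second satisfies the first. It is loose wording and not part of this point.

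**Conclusion.** The point holds in this form. What the article labels catch per unit effort is monthly catch of fish of all sizes. It serves as one of two unlinked indicators of a primary outcome about mature fish, with no statement of which decides Hypothesis 7. The contradiction between label and formula and the missing maturity limit are plain from the text and rest on no assumption. That the indicator can move against catch per day (+20% against −10%) or against mature catch (−15% against +20%) rests on assumed values. The actual size cannot be derived from the documents. Because a primary hypothesis depends on it, the definition should be corrected before analysis.

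**What to change.** 1. Name one primary indicator for Hypothesis 7: mature catch per fisher-trip, or per fisher-day. A trip basis matches the revenue outcome. Trap-sets are not listed as recorded, so they should not be the denominator unless they are added to data collection.
2. State how it is derived: scale the 20-fish length sub-sample to the trip's catch using stated maturity lengths. If it is expressed by weight, add a length-weight conversion, since only lengths are described for the sub-sample. Include a rule for fish identified only to genus.
3. Analyse it with allowance for clustering by landing site or BMU. Trips should not be treated as independent.
4. Report average daily catch times days fished separately as total monthly catch, and drop the per-unit-effort label from it.

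If the investigators prefer a monthly target, monthly mature yield would also fit the wording of Hypothesis 7, provided that it is named as such and effort is accounted for.

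The cost is modest. Catch weights, identifications and sub-sample lengths are already planned. The additions are some analysis work and dependence on published maturity and length-weight values, which bring their own uncertainty.

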#### Secondary outcomes

##### Child diet diversity

The Child Dietary Diversity Score (CDDS) will be calculated using the total number of food groups reported in the food frequency intake portion of the survey. We will use WHO defined food groups: (1) grains, roots, and tubers; (2) legumes and nuts; (3) dairy products (milk, yogurt, cheese); (4) flesh foods (meat, fish, poultry, and liver/organ meats); (5) eggs; (6) vitamin A rich fruits and vegetables; and (7) other fruits and vegetables. If new indicator guidelines are released before data analysis activities of this project are undertaken, we will apply the new definition.

*Diarrheal morbidity* will be calculated using a standard 2-week recall conducted during the household survey and home visits. Questions will assess diarrheal severity including the frequency of diarrhea in the children, presence of blood or fever, use of antimicrobials, and requirement for additional medical care at a clinic or local provider. This data will be used to estimate indicators for acute diarrhea (3 or more liquid or semi-liquid stools in a 24-h period over the last 2 weeks) and persistent diarrhea (lasts 14 days or longer).

##### Fisher revenue

During fisheries yield data collection, enumerators will also ask fishers about their operational costs and the revenue generated from selling the fish. Fisher revenue will be represented as Kenyan shillings (Ksh) per fishing trip. These questions will be informed by cultural norms and objects such as food and equipment used as currency when Kenyan shillings cannot be estimated (e.g., bags of rice). Comparisons will be made at the landing site or BMU level to measure the change in earnings pre- and post-intervention as described by Wamukota et al. (35).

A range of other variables will be assessed to control for cofounding factors associated with the cluster design. These variables include but are not limited to child illness (a standard 2-week recall on infectious illnesses including cough, rhinorrhea, fever, and rash), household consumption and assets, and household decision making [Likert scale instrument that captures common domains of decision-making including purchasing decisions; decisions regarding service use (health, education); decisions regarding children's diet, health and education].

#### Process evaluation

As shown in Table 6, the process evaluation will examine three key implementation outcomes: fidelity, adoption, and sustainability. The *fidelity* outcome will capture the degree to which the intervention was implemented as described in the study protocol, adherence over the course of the intervention, and the quality of program delivery (33). Methods for collecting and documenting implementation fidelity include activity/event counts, semi-structured interviews with intervention participants, reports from the field team, and a baseline/endline survey of caregivers and fishers that assess awareness and knowledge transfer associated with the social marketing campaign.

**Table 6 T6:** Process evaluation outcomes.

**Outcome**	**Methods**	**Data collected**	**Timepoints**
Fidelity	Counts of activities/events Activity/event sign-in sheets	Age of the participant/s, sex (M/F), date, material that was distributed	Rolling basis as activities/events are conducted
	15–20 semi-structured interviews with caregivers and fishers	Project materials viewed Messages that they are aware of Perceptions of the materials and messages Challenges understanding the messages What worked well, what could be improved	6–9 mo.
	Semi-structured discussions pre/post activities	What was learned What worked well, what could be improved	6–9 mo.
	Field team reports	Reports detailing implementation of activities	6 mo., 12 mo.
	Household/fisher survey	Awareness of nutrition messaging	Baseline, 12 mo.
Adoption	Caregiver home visits	Intentions to try, actions since last visit, observations	3, 6, and 9 mo.
	Household/fisher survey	Knowledge transfer linked to the social marketing campaign	Baseline, 12 mo.
	Meetings with fishers	Self-reported use of traps, intentions to try	6–12 mo.
Sustainability	15–20 semi-structured interviews with key informants	What they know about the intervention Perceptions, feasibility for maintaining it once the intervention ends	12 mo.

*Adoption* will focus on better understanding participants intention to try to actualize the information they receive (33). During home visits with caregivers the research team will observe what changes the mother/caregiver has made and their intention to try to act on the messaging in the future. Meetings with fishers will gather similar information as well as asking fishers to report on their use of the modified traps.

The *sustainability* outcome is intended as an initial assessment of local institutions interest and ability to maintain the intervention once it has been completed. Semi-structured interviews with BMU officials, heads of local health clinics, CHVs, and other relevant local government representatives will be used to assess what they know about the intervention, their perceptions of it, and institutions interest and potential for maintaining.

### Analysis

#### Primary and secondary outcomes

Generalized linear regression modeling (GLM), allowing for non-normal distributions, will test the continuous outcomes of HAZ, WAZ, child dietary fish intake, child dietary diversity score, fisheries yield, and fish earnings. As a difference-in-difference analyses, change variables for each outcome will be examined (difference between baseline and endline). For the binomial outcomes of diarrhea morbidity (and other outcomes of stunting and underweight), we will estimate prevalence ratios by the GLM modeling with robust Poisson. If stunting prevalence in this population exceeds the acceptable threshold for use of odds ratios (0.2105), prevalence ratios (PRs) will be used to examine the intervention effect and were considered analogous to relative risk in this longitudinal study. The robust Poisson, with a classic sandwich estimator to correct the inflated variance of standard Poisson, is less affected by outliers.

To test for intervention effectiveness, the two intervention groups will be combined for all hypotheses except the secondary outcome of increased fisher earnings and exploratory hypothesis for differences between social marketing and social marketing + traps intervention groups. Regression models will be adjusted for potential confounding factors including age, sex of the child, corresponding baseline measures, and others found to differ significantly between the trial groups (e.g., maternal education). For fisheries yield, confounding factors will be used to adjust regression models, such as: water temperature, fishing ground area, coral cover, and seasonality. The *P* significance value for Type I error (and one-tailed test) will be *P* < 0.05 and corresponding 95% confidence interval. Diagnostics for regression model assumptions, structure and observations will be applied, and corrective procedures applied as necessary. If selection bias is widely detected with important differences across intervention and control communities, we will apply propensity score analyses (36). Data analyses will be performed with Stata software (version 16.0; StataCorp, College Station, TX) and R (4.1.2).

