**Methods:**

There will be 400 small-scale fisher households enrolled from Kilifi County, Kenya and residing in communities matched on location (rural), livelihoods, and child nutritional status. The sample will include mothers and other caregivers, children 6–60 months, and fishers in the family. Applying a cluster design, the matched communities will be divided into three groups: (1) control (*n* = 200); (2) multi-component nutrition social marketing intervention to fishers, mothers, and health workers (*n* = 100); and (3) multi-component nutrition social marketing intervention plus modified fishing traps and training (*n* = 100). Primary outcomes include child growth, fish food intakes, and fisheries yield of mature fish. Secondary outcomes are diet diversity, child diarrheal morbidity, and fisheries revenue. A process evaluation will be used to monitor and ensure fidelity of intervention delivery.

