### Sample size

Sample size calculations for the cluster design applied a mean −1.3 height-for-age (HAZ) for the coast region (20) and a hypothesized 0.20 effect size (21). Thus, we estimate requiring a total sample size of 400 households, which includes ~4 clusters per arm (four villages per BMU) and 50–75 households per cluster – assuming 20% losses-to-follow-up (α = 0.05 and 1-β = 0.80). Although this is small number of clusters, we will apply matching techniques a priori and during data analyses (e.g., propensity score matching) to better ensure internal validity.

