### Participant eligibility, recruitment, and retention

At the outset of the study, we will identify comparable communities associated with BMUs on the coast of Kilifi County using potential confounding variables: proximity to shoreline or ability to participate in the fishery; presence of no-take fisheries closures; composition of fishing gears used; background nutritional status; usual diets; income and assets; and access to market information. We will draw on existing relationships and data from communities where formative research was previously conducted by the project team. BMU leaders and other stakeholders will be convened to first inform them of the potential project and solicit permission to act in partnership with BMUs to conduct the research.

To be eligible to participate in the study, an individual must meet all of the following criteria:
A household member works in small-scale fisheries (self-employed fishers).At least one child in the household aged 6–60 months.Provision of signed and dated informed consent form.For children, informed assent and parental informed consent to participate in the study.Stated willingness to comply with all study procedures and availability for the duration of the study.

An individual who meets any of the following criteria will be excluded from participation in the study:
No household member works in small-scale fisheries (self-employed fishers).No child in the household aged 6–60 months.Declines to sign the informed consent.Index child is severely malnourished.Lives outside the study area.Participation in another nutrition or fisheries intervention study within April 2021 - June 2022.

We anticipate a total sample size of 400 small-scale fisher household units (mother, father, and child 6–60 months). There will be 100 in each intervention group (social marketing and social marketing plus modified traps) and 200 in the control group. Table 2 provides a summary of the total number of individuals and anticipated demographics.

**Table 2 T2:** Sample size and demographics.

**Group 1: Control (n = 200)**			**Group 2: Social marketing (n = 100)**			**Group 3: Social marketing + modified traps (n = 100)**		
**Group**	**# of individuals**	**Anticipated sex**	**Group**	**# of individuals**	**Anticipated sex**	**Group**	**# of individuals**	**Anticipated sex**

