**Total sample size: 400 total households**								
Mother/caregiver	200	Female	Mother/caregiver	100	Female	Mother/caregiver	100	Female
Fisher	200	male	Fisher	100	Male	Fisher	100	Male
Children 6–60 months	Minimum of 200	Mixed	Children 6–60 months	Minimum of 100	Mixed	Children 6–60 months	Minimum of 100	Mixed

Participant recruitment and enrollment will be conducted by the two Kenyan partner universities (Egerton University and Pwani University). Pwani University, located in Kilifi County and on the coast, is well-positioned to be in continuous interaction with community stakeholders. The Kenya P.I. from Pwani has established relationships in Kilifi over many years of working there and teaches many university students from the neighboring fishing villages. Additionally, the US Co-P.I. from the University of Rhode Island (URI) has worked in this area for over 10 years conducting research on coral reef fisheries management and has long-term working relationships with fishers and BMU leaders. The Kenya Co-P.I. from Egerton University was involved in formative research along the coast and has made contacts with local health care workers and clinics for collecting data and measuring nutrition outcomes.

Recruitment efforts will begin with consultations with key community stakeholders including BMU leaders and board representatives; health care workers in local clinics; community health workers (CHVs); religious leaders; municipal administrators. With their agreement, communities will be matched based on the closest set of characteristics and assigned to control and intervention groups.

Retention efforts will be primarily carried out in tandem with the social marketing campaign. Activities to increase participant engagement – both in control and intervention groups – will include meetings, social gatherings, and project materials (e.g. T-shirts, flyers, lifejackets). These efforts are modeled from the Lulun Project in Ecuador (25) and adapted to the Kenyan context should help retain participants.

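### Whole communities are allocated, but the models stated for the child outcomes make no allowance for that unit, so their errors are understated unless the residual intracluster correlation is near zero

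*Protocol article*

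**What the plan says.** The Abstract describes the allocation: "Applying a cluster design, the matched communities will be divided into three groups". The section on participant eligibility, recruitment and retention confirms that "communities will be matched based on the closest set of characteristics and assigned to control and intervention groups". The Sample size section gives "4 clusters per arm (four villages per BMU) and 50–75 households per cluster", the cluster count being marked as approximate, and the total: "we estimate requiring a total sample size of 400 households". On how few clusters there are, it says: "Although this is small number of clusters, we will apply matching techniques a priori and during data analyses", with propensity score matching as its example.

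The Analysis section (Primary and secondary outcomes) then fixes the models.
- Continuous outcomes: "Generalized linear regression modeling (GLM), allowing for non-normal distributions, will test the continuous outcomes of HAZ, WAZ, child dietary fish intake". The list goes on to dietary diversity, fisheries yield and earnings. Change from baseline to endline is the analysed variable.
- Binary outcomes: "The robust Poisson, with a classic sandwich estimator to correct the inflated variance of standard Poisson".
- Covariates for the child models: age, sex, baseline value and characteristics that differ between groups.
- Test: one-tailed at 0.05, with the two intervention groups pooled for most hypotheses.

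No random effect, GEE, cluster-robust variance, cluster-level summary or small-cluster correction is stated for HAZ, WAZ, fish intake, dietary diversity or diarrhoea. For fisheries, the Study measures text on yield looks at changes by landing site or BMU, and the text on fisher revenue compares earnings at that level.

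**The concern.** Children in one village share landing sites, markets, health workers, seasons and, in the intervention arms, the same workshops and demonstrations. Their changes over 12 months are therefore likely to be correlated. When the village or BMU is what gets allocated, the information about the intervention is limited by the number of such units, not only by the number of children. A model that treats children as independent gives a standard error that is too small, and ordinary variation between villages can then be reported as an effect on growth or diet.

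The remedies in the plan answer a different question. Matching and propensity scores make the groups more alike at the start. Difference-in-difference removes stable village differences. Neither removes a village-level shock during follow-up, and neither changes how the standard error is computed.

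**Working it through.** **Inputs from the article.** 400 households, split 200 control, 100 and 100; about 4 clusters per arm; 50–75 households per cluster; 20% loss; effect 0.20 HAZ; alpha 0.05; power 0.80; one-tailed test in the Analysis section. No SD and no ICC are given, so both are assumptions below.

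**The plan's own figure.** 400 cannot be reproduced without an SD. After 20% loss each side of the pooled comparison has 200 × 0.8 = 160 children. With no clustering, 80% power needs SD = 0.20 × √(160/2) / (z for alpha + 0.842):
- one-tailed: 1.789 / (1.645 + 0.842) = 0.72
- two-sided: 1.789 / (1.960 + 0.842) = 0.64

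**Layout.** 2 × 4 × 50 = 400 fits four clusters on each side. Three arms with four clusters of 50 would be 600. The total of 400 can still be met with 8 intervention clusters of 25 against 4 control clusters of 50. After loss the two layouts are 4 v 4 of 40, and 8 of 20 v 4 of 40. Both are used.

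**Effect of ignoring clustering.** Design effect DE = 1 + (m − 1) × ICC. For 4 v 4 of 40, DE = 1 + 39 × ICC. For 8 of 20 v 4 of 40, with 160 children on each side, DE is the average of 1 + 19 × ICC and 1 + 39 × ICC, which is 1 + 29 × ICC. The true standard error is √DE times the model's. The real one-tailed error is 1 − Φ(1.645/√DE).

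| Assumed ICC | DE, 4 v 4 | SE ratio | Real one-tailed error, 4 v 4 | DE, 8 v 4 | Real one-tailed error, 8 v 4 |
|---|---|---|---|---|---|
| 0.01 | 1.39 | 1.18 | 8.1% | 1.29 | 7.4% |
| 0.02 | 1.78 | 1.33 | 10.9% | 1.58 | 9.5% |
| 0.05 | 2.95 | 1.72 | 16.9% | 2.45 | 14.7% |

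At ICC 0.005 (4 v 4), DE = 1.195 and the error is 6.6%. With 75 per cluster and no loss, the three errors are 10.6%, 14.8% and 22.4%.

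**Intervals.** For 4 v 4, the two-sided error is 9.6%, 14.2% and 25.4%, so a nominal 95% interval covers about 90%, 86% and 75% of the time.

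**Simulation check.** In 20,000 runs (4 v 4, 40 each) the one-tailed error of the naive test was 8.1%, 10.9% and 16.9%. A t-test on cluster means (6 df) on the same data gave 4.7% to 4.9%.

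**Power once clustering is respected.** Take SD 0.72, the value at which 400 households give 80% with no clustering. The one-tailed cluster-mean t-test then has power 0.71 at ICC 0, and 0.59, 0.50 and 0.36 at ICC 0.01, 0.02 and 0.05.

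**The case against.** The strongest defence is that this is a condensed article, and that random-effect structure and degrees of freedom belong in an analysis plan not shown here. That would hold if the article were silent. It is not: it names the model, the variance estimator, the covariates, the direction of the test and the software, and it answers the shortage of clusters with matching. The promise of model diagnostics and corrective action is generic and commits to no cluster method.

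Other parts of the defence stand, and they rule out stronger readings that a reader might infer.

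- **That every model ignores the site.** The yield and revenue text describes landing-site or BMU comparisons, and the yield model has site-type covariates. The fault there is that two sections do not agree on the unit.
- **That repeated fishing trips make the fisheries tests worse.** The Analysis section specifies change variables for each outcome. Read literally, trips do not enter as independent observations, and no such effect was computed.
- **That omitting a matched-set term shrinks the standard error.** Ignoring effective matching normally makes it too large.
- **That the sandwich is certainly computed per child.** The level is not stated. Its only stated purpose is to correct the Poisson variance, which makes that reading likely but not certain.
- **That the inflation is a known quantity.** Differencing, baseline adjustment and matching can all lower the relevant ICC, and the simulation included none of them.

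**Conclusion.** The point holds for HAZ, WAZ, fish intake, dietary diversity and diarrhoea: the stated analysis does not match the unit of allocation. For yield and earnings the conclusion is narrower: the sections must be reconciled on the unit of analysis.

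The size is conditional on the assumed ICC of the analysed, adjusted change. Across 0.01 to 0.05 the real error of the 5% test is roughly one and a half to more than three times nominal. At 0.005 the excess is small, and at zero it vanishes. The article claims no such near-zero value. Because four villages are mentioned per BMU and five study areas are listed, the cluster could be the village or the BMU. If allocation is by BMU, there are fewer independent units and the problem grows.

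This should be fixed before analysis, because it reaches the primary growth and fish-intake tests.

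**What to change.** In the Analysis section:

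1. Name the allocation unit (village or BMU) and the number of units on each side of the pooled comparison.
2. For continuous child outcomes, pre-specify one cluster-valid analysis with a small-sample correction. Either a mixed model with a single cluster random intercept and Kenward–Roger or Satterthwaite degrees of freedom, or a t-test on cluster-level mean changes, would do. Some 8 to 12 clusters will not support several nested random terms, and an uncorrected cluster sandwich is itself too liberal at that number.
3. For diarrhoea and other binary outcomes, use modified Poisson with a bias-corrected cluster-robust variance.
4. For yield and earnings, state the unit of analysis once and make the Analysis and Study measures sections agree.
5. Report the estimated ICC for each primary child outcome.

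In the Sample size section, restate power with the SD, the ICC and the cluster layout.

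The programming is modest in Stata or R. The real cost is wider intervals and power that is likely to be below the stated 80%, which should be acknowledged before the data are seen.
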